#### PCT-guided therapy

PCT-guided therapy applies to neonates born at 34 weeks of gestation or later, who at 12 hours after start of antibiotics (t=12) are classified as having low or medium risk of infection (Group 1) based on the presence of one or two abnormal findings among the following categories: risk factors, clinical symptoms and laboratory findings (online supplemental file 1, table S1). PCT levels are assessed at t=12 (±6 hours) and t=24 (±6 hours) with a minimum of 12 hours between the measurements, and if consecutive values fall within the reference interval of the age-adjusted nomogram (online supplemental file 1, figure S1), antibiotic therapy can be discontinued as early as the second PCT value is known. For neonates without two consecutive low values of PCT, for neonates that are classified as high risk (Group 2), and in case PCT is not available, the necessity of treatment is reassessed at t=36 based on clinical course and blood culture following current practice. In neonates with blood culture proven infection, treatment will always be continued for at least 7 days, targeting the pathogen.

#### IV-to-oral switch therapy

IV-to-oral switch therapy applies to neonates born at 34 weeks or later, with a birth weight of >2000 grams, who are still suspected of infection, despite a negative blood culture, based on clinical symptoms/risk factors and abnormal infection parameters at the discretion of the paediatrician. After 36 hours of intravenous antibiotic therapy, if the neonate tolerates oral (tube) feeding and is clinically well, treatment is switched to oral antibiotic therapy with amoxicillin suspension. The recommended daily dose will be according to the Dutch Paediatric Formulary, 60 mg/kg/day in two doses, based on recently published data.^31^ In case the neonate vomits within half an hour of ingestion, administration should be repeated. The first dose will always be administered in the hospital, to assess tolerance by the neonate and educate parents. Afterwards, the location of treatment will shift from the hospital to the home environment in case this is considered safe. The paediatrician will stay responsible for neonatal care during the entire treatment period; care will not formally be transitioned to primary care. Nevertheless, informing primary care professionals about antibiotic treatment of the neonate is an essential part of the discharge procedure, as they are often a first contact person for families in the maternity period.

### Implementation strategy

#### Implementation mapping

We developed an implementation strategy, built of several sub-strategies, to facilitate implementation of the antibiotic stewardship interventions. The strategies were created by Implementation Mapping to design strategies with potential for successful real-world application. Implementation Mapping is distinct from intervention mapping and adapted to fit for design of implementation strategies.^32^ We combined the updated Consolidated Framework for Implementation Research to collect influencing determinants and the Taxonomy of Behavioural Change Methods to inform development of the strategies.^33 34^ All steps of the implementation mapping process are described in online supplemental file 2, tables S2–S4. Figure 2 gives a summary of determinants, implementation strategies, mechanisms and outcomes. Figure 3 gives an overview of the timeline per implementation strategy component.

**Figure 2 F2:**
[figure not shown]
Implementation research logic model. Determinants are divided into barriers (red) and facilitators (green). DOTs, days on therapy; E, early-onset sepsis calculator; EHR, electronic health record; EOS, early-onset sepsis; IV, intravenous; O, IV-to-oral switch therapy; P, procalcitonin-guided therapy; PCT, procalcitonin.

**Figure 3 F3:**
[figure not shown]
Implementation strategy components per study period. The symbol (**x**) indicates the specific time point at which a component is executed, while (→) represents the continuation of the practice beyond the active implementation period. EHR, electronic health record; EOS, early-onset sepsis.

### Implementation strategies

#### Strategy 1: Appointment of local implementation team and task list

Per site, an implementation team will be appointed, consisting of at least one nurse champion and two paediatrician champions (early adopters) that are tasked with leading implementation of the interventions within their hospital and its associated neonatal care network. The appointed implementation champions are respected individuals within the organisation who have the ability to motivate and engage their colleagues and have positive attitudes regarding the interventions. The implementation team will be briefed by the central study team and will be provided with a list of tasks and responsibilities. First, they will work towards their department’s adoption of the antibiotic stewardship interventions by (1) briefing and discussing the interventions with the paediatric specialist group and microbiologist, (2) reviewing resource availability with the clinical chemistry laboratory (PCT determination equipment) and pharmacy (amoxicillin suspension), (3) informing and engaging the obstetric department and obstetric partnerships and (4) adapting local medical and nursing guidelines to incorporate the interventions. Second, the implementation team supports implementation during the entire rollout of the project, by sharing their knowledge, reminding colleagues to adhere to the interventions and serving as primary point of contact for colleagues. To assist the local champions in discussing availability of resources and engaging stakeholders, the central research team provides tailored scientific information on PCT costs and IV-to-oral switch therapy, as well as a fact sheet with information about the intervention for the obstetric partnerships, if required. Moreover, the protocols of the antibiotic stewardship intervention will be made available in separate modules by the central research team, to facilitate integration of the interventions in the local protocol independently of each other.

#### Strategy 2: Paediatric education-discussion kick-off session and ready-to-use presentation template

Each local implementation team will organise a kick-off education-discussion session for the paediatric (resident) specialist team. The central research team facilitates a standardised presentation format to present data of current practice and room for improvement, followed by a concise overview of the evidence and practical application of the EOS calculator, PCT-guided therapy and IV-to-oral switch therapy. Subsequently, discussion will be encouraged by presenting potential pitfalls and actively asking for the participants’ perspectives. Afterwards, the presentation will be available for all paediatricians and paediatric residents, to be used for reference or reading in case of absence during the session. If required, the education discussion session can be repeated by the local implementation leader. The paediatricians and paediatric residents will be asked to sign off when they have attended the session, or gone through the information independently.

#### Strategy 3: Evidence-based podcast series on early onset sepsis

Five podcast episodes will be released, featuring experts and role models discussing essential topics regarding EOS. All scientific evidence discussed during the episodes will be linked in the show notes. The podcast is primarily focused on paediatricians and paediatric residents, but will also provide valuable information for microbiologists, pharmacologists, gynaecologists and neonatal nurses. The local implementation champions will actively send the link of each episode to their colleagues. The podcast will be shared on the publicly available free streaming Spotify, as well as the project’s website (http://www.neoinfecties.nl/).

#### Strategy 4: Nurse education leader and ready-to-use presentation template

Per site, one or more nurses will be appointed by the local implementation team as responsible for educating the nursing staff. These nurse education leaders will educate their peers on the antibiotic stewardship interventions through bedside teaching, conducting online or live educational sessions or providing an instructional email. A ready-to-use presentation will be available for the responsible nurses to use during education and to disseminate to all other nurses. All nurses are asked to sign off once they have received education on IV-to-oral switch therapy.

#### Strategy 5: Facilitation of EOS calculator integration in the electronic health record

In hospitals using the HiX (Chipsoft) electronic health record (EHR), the EOS calculator will be integrated directly into the patient record, eliminating the need to access it externally. The central research team will coordinate with Chipsoft to ensure the availability of the HiX calculator at participating sites and will provide an instruction manual for actually activating and using the calculator in practice. In hospitals not using HiX, a link to both the Kaiser Permanente website and the published open-source version of the EOS calculator will be provided, ensuring hospitals are not dependent on logistical, technical or maintenance issues associated with the Kaiser Permanente website.^35 36^

#### Strategy 6: Primary care maternity nurse knowledge module and newsletter

A targeted informative module on IV-to-oral switch therapy will be made available for all primary care maternity nurses on the National Knowledge Centre of Maternity Care’s website’s database (http://www.kckz.nl/), which is the formal website of Dutch maternity care guidelines. This module will cover general background information on EOS and IV-to-oral switch therapy, along with detailed information on care responsibilities, the instructions provided to parents regarding antibiotic administration, safety precautions and contact information. Additionally, this document, including further explanations, will be distributed to all maternity nurses through the KCZK’s email newsletter.

#### Strategy 7: Parent-guided practice, instruction leaflet and medication scheme checklist

Every parent taking a neonate home on oral antibiotic therapy will receive training from a neonatal nurse on antibiotics administration. After receiving instructions, parents will practise administering at least one dose in the hospital under the nurse’s guidance. In addition, a template for an instructional parent leaflet will be provided to all participating sites, allowing for adaptation to local communication needs and contact information. Parents will receive this instruction leaflet from the neonatal nurse at discharge. This includes detailed guidance on how to administer the antibiotics, steps to follow if a dose is missed or if the neonate vomits, warning signs and contact information for the hospital. The folder is available in both Dutch and English and written at a B1 language level. Additionally, a time schedule checklist is included, where the nurse or paediatrician will note the exact times and days for administering each dose at home. Parents are encouraged to use this checklist as a memory aid throughout the course of treatment.

#### Strategy 8: IV-to-oral switch therapy parental instructional video

An instructional video explaining oral antibiotic therapy, administration instructions, safety measurements and reasons to contact the neonatal department in case the neonate is at home will be made publicly available on a free streaming platform as well as the project’s website (http://www.neoinfecties.nl/), both in Dutch and English. This video primarily targets parents who go home with their neonate on oral antibiotics and is linked via a QR code on the parent instructional folder that every parent will receive at discharge. However, the video also serves as an educational source for neonatal nurses and maternity nurses and can support them in instructing parents.^34 35^

### Study outcomes

This study’s outcomes and their definitions have been streamlined as much as possible with those reported in literature, to pursue uniformity in data. Clinical outcomes are based on the Center for Disease Control and Prevention’s definitions for tracking antibiotic use and resistance and on the AENEAS (Analysis of Antibiotic Exposure and Early-Onset Neonatal Sepsis in Europe, North America, and Australia) study group’s proposed key indicators for reporting data on EOS and antibiotic use.^1 37^ Implementation outcomes are mainly based on Proctor’ taxonomy of implementation outcomes.^38^ All outcomes and their definitions are described in detail in online supplemental file 3, table S5.

#### Primary outcome

The primary outcome of this study is the total exposure to antibiotic therapy that was initiated within the first 72 hours after birth for the treatment of EOS. The exposure is measured in days on therapy (DOT), where a therapy day is defined as any calendar day when at least one dose of any antibiotic is administered. Besides the days on any antibiotic, also DOT per individual antibiotic agent (type and administration route) will be measured.

#### Secondary implementation outcomes—antibiotic stewardship interventions

We will determine the adoption of the three antibiotic stewardship interventions on department level. The fidelity to the antibiotic stewardship strategies will be determined on patient level, by calculating the proportion of eligible patients in which the intervention was applied. Professionals’ reported feasibility and acceptability of the interventions will be assessed to understand levels of adoption and fidelity and to inform possible future refinements of the interventions.

#### Secondary outcomes—process evaluation of multimodal implementation strategy

We will evaluate the process of implementation to analyse to what degree the implementation was successfully executed. Fidelity to the different implementation strategies will be measured, including detailed registration of potential ad hoc local adaptations of the strategy. The appropriateness of the different implementation strategies will be evaluated to determine their relevance and inform potential future improvement.

#### Secondary outcomes—clinical

We will determine the proportion of neonates starting on antibiotics per 100 live births, proportion of neonates receiving antibiotics per predefined category of duration (36 hours, 36–48 hours, 48–72 hours, >5 days and >7 days), duration of therapy, proportion of neonates receiving IV-to-oral switch therapy, duration of hospital stay, cumulative number of laboratory tests, cumulative readmission rate within 28 days after birth, cumulative bacterial (re)infection rate within 28 days after birth, incidence of culture-proven EOS per 1000 live births, pathogen determination and antibiotic susceptibility and infection-related mortality within 28 days after birth. For all (re)infections, we will provide exact data on timing of the infection within the first 28 days as well as the pathogen determination.

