#### Data from the electronic health record

Data will be collected using automated data extraction methods of the hospitals’ business intelligence unit. Data will be sampled from all neonates with suspected EOS who were started on antibiotics during the pre- and post implementation period and include gestational age, birth weight, initiation of antibiotic treatment within the first 3 days of life, names and dosages of antibiotics used, duration of antibiotic treatment, blood culture results with pathogen identification, CRP and procalcitonin values within the first 28 days of life, readmissions within 28 days after discharge, re-initiation of antibiotic therapy within 28 days and discharge destination (home or transfer to another hospital). Additionally, the total number of live births during both periods will be obtained from hospital registries. All data will be securely stored in the Castor Electronic Data Capture (EDC) system.

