#### Sample size

Estimating the median DOTs in the Netherlands during the pre-implementation period is challenging due to the lack of data on the exact duration of antibiotic treatment for EOS in Dutch neonates. However, a mean antibiotic initiation rate of 3.8% of all live-born neonates was reported in 13 secondary Dutch hospitals.^40^ Additionally, another study among Dutch hospitals found that antibiotics were continued intravenously for more than 72 hours in 31.5% of cases in.^41^ Since neonates in the Netherlands are usually treated for either 24–72 hours (average 2 days) or 7 days, we can estimate the pre-implementation DOTs to be 136 per 1000 live-births (calculated as follows: (0.685×38 neonates×2 days) + (0.315×38 neonates×7 days)). This estimate matches the mean antibiotic exposure in other high-income countries, which is 135 (range 54–491) DOTs per 1000 live births as reported in the AENEAS study.^1^ Our goal for the post implementation period is to reduce the antibiotic initiation rate to 2% and halve the number of full treatment courses, aiming for 60 DOTs per 1000 live-births. However, we consider a reduction of at least 10% of DOTs to be clinically relevant. This would result in a post implementation outcome of 121.5 DOTs per 1000 live-births. Assuming a power of 90% and an alpha of 5%, a sample size of 2790 (1395 per group) would be required. This sample size will be feasible for both the total study population and most individual sites, since Dutch hospitals typically report annual birth rates ranging from 1000 to 3500, averaging approximately 2500 births per hospital per year. However, in hospitals with already low pre-implementation DOTs, no differences in absolute DOTS or trends may be found. This is acceptable, as this would demonstrate that these hospitals are already leading in the reduction of antibiotic use, and finding a difference through greater sample size would not be clinically relevant.

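### Readmission is not like-for-like before and after implementation in the first ten days or so, because the bundle changes who is at home to be readmitted

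*Protocol article*

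**What the plan says.** In the protocol article, Secondary outcomes—clinical lists "cumulative readmission rate within 28 days after birth" among about a dozen unranked clinical outcomes. Under Analysis, Secondary outcomes, categorical outcomes are compared between the two periods with a chi-square or Fisher test.

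The Sample size section describes care before implementation. It cites a study in which "antibiotics were continued intravenously for more than 72 hours in 31.5% of cases", and says that neonates are "usually treated for either 24–72 hours (average 2 days) or 7 days".

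The section IV-to-oral switch therapy describes care after implementation. The switch applies to neonates with a negative blood culture who are still suspected of infection. Its timing is "After 36 hours of intravenous antibiotic therapy, if the neonate tolerates oral (tube) feeding and is clinically well". After a first oral dose in hospital, "the location of treatment will shift from the hospital to the home environment in case this is considered safe".

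Data from the electronic health record restricts the sample to neonates who were started on antibiotics, and it extracts "readmissions within 28 days after discharge, re-initiation of antibiotic therapy within 28 days". The readmission window there starts at discharge, whereas the outcome list starts it at birth.

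**The concern.** A readmission needs a prior discharge, and the bundle is designed to bring discharge forward for part of the long-course group. A neonate who worsens on day 5 while on a 7-day intravenous course is on the ward and cannot be readmitted. A similar neonate who worsens on day 5 at home on oral treatment can be. The readmission count therefore changes with place of care even if the risk of worsening does not.

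Readmission is a natural thing to look at when treatment moves home. As defined, a modest rise could reflect relocated events, and an unchanged rate would not be a clean reassurance either. Nothing in the article counts an in-hospital equivalent of a readmission or adjusts for time out of hospital.

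**Working it through.** **The plan's own figure.** Sample size starts from a "mean antibiotic initiation rate of 3.8% of all live-born neonates", i.e. 38 per 1000, and the 31.5% split: 0.685 × 38 × 2 + 0.315 × 38 × 7 = 52.06 + 83.79 = 135.85. This reproduces the stated 136 days of therapy per 1000 live births. The same split gives 0.315 × 38 ≈ 12 long courses and 0.685 × 38 ≈ 26 short courses per 1000 births. Relocation can thus affect at most 31.5% of treated neonates.

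**Assumptions not in the documents.** Discharge is at day 2 after a short course in both periods, at day 7 after a long course before implementation, and at day 2 after a switch. All long courses are switched and sent home. Course mix and true risk are unchanged, and risk is equal in both course groups. The article gives no readmission rate, discharge day or event timing.

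**Model 1, window to day 28 after birth.** Let s be the share of a long-course neonate's day 2–28 events that fall on days 2–7. For a constant rate, s = 5/26. For exponential timing with mean m days, s = (1 − exp(−5/m)) / (1 − exp(−26/m)). The apparent ratio over all treated neonates is 1/(1 − 0.315s).

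| Event timing | s | 0.315 × s | Overall ratio |
|---|---|---|---|
| constant | 0.192 | 0.061 | 1.06 |
| mean 18 days | 0.317 | 0.100 | 1.11 |
| mean 10 days | 0.425 | 0.134 | 1.15 |
| mean 7 days | 0.523 | 0.165 | 1.20 |

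Within the long-course group the ratio 1/(1 − s) runs from 1.24 to 2.10.

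**The same model, window of 28 days after discharge.** With a constant rate both periods have 28 days at risk and the ratio is 28/28 = 1.00. With exponential timing the share lost is 1 − exp(−5/m) = 0.243, 0.393 and 0.510 for means of 18, 10 and 7 days. The overall ratios 1/(1 − 0.315 × share) are 1.08, 1.14 and 1.19. The constant-rate effect therefore comes only from stopping the count at day 28 of life; the early-clustering effect remains under either window.

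**Model 2, partial uptake.** Let f be the fraction of long courses that is at home. The day 2–7 component is multiplied by (0.685 + 0.315f)/0.685, which is 1.11, 1.23, 1.34 and 1.46 for f = 0.25, 0.5, 0.75 and 1. Now add a later readmission risk that is equal in both periods. At f = 1:

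- day 2–7 risk 1%, later risk 5%: 5.69% to 6.00%, ratio 1.06
- day 2–7 risk 2%, later risk 2%: 3.37% to 4.00%, ratio 1.19
- day 2–7 risk 5%, later risk 2%: 5.43% to 7.00%, ratio 1.29

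**Absolute size.** At 11 sites with about 2500 births each, 11 × 2500 × 0.038 = 1045 neonates are treated per period, of whom 0.315 × 1045 ≈ 329 have long courses. Day 2–7 risks of 1%, 2% and 5% give about 3, 7 and 16 relocated events at f = 1, and about half that if full courses are halved as the plan intends. With 1045 per period and a 2% later risk, the chance that relocation alone gives p < 0.05 is about 6%, 12% and 32%.

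**The case against.** A reader might infer that an early failure leaves no trace at all before implementation. The documents do not support that. Bacterial (re)infection within 28 days after birth with exact timing, infection-related mortality, duration of therapy and length of stay are compared in both periods, and each can register a failure on the ward. They do so only in part: duration and stay are meant to fall under the bundle, so they cannot isolate failures, and mortality captures only the extreme. Whether (re)infection includes culture-negative cases cannot be told, because the definitions are in supplementary table S5, which is not shown. That table could also hold an in-hospital equivalent.

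A reader might also infer that the safety comparison as a whole is biased against the bundle. That does not follow. Only neonates started on antibiotics are sampled, so one left untreated under the EOS calculator and later readmitted is not counted, which works the other way. The intended fall in initiation from 3.8% to 2% also changes the denominator and the case mix.

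Finally, readmission is one unranked secondary outcome with no margin attached, going home is conditional, and the 68.5% on short courses are little affected by the switch. All of this stands. It limits the size and weight of the point but does not make the early part of the readmission count comparable.

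**Conclusion.** The point holds as a cheap improvement. Readmission within 28 days after birth is not comparable between periods in the first days of life, because part of a group of up to 31.5% of treated neonates moves from ward to home. With no true change in risk, the apparent overall ratio is about 1.06 to 1.20 with the window counted from birth. This rests on assumed event timing and on every long course being switched and sent home. It is an upper bound on uptake, since culture-proven cases are not switched. A different model with assumed risks gives up to 1.29 at full uptake with a 2% later risk, and less at partial uptake.

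The constant-rate part disappears if the window runs from discharge, so the size depends on a definition that the article leaves inconsistent. This component alone pushes readmissions up after implementation; the net direction across all biases is not established.

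**What to change.** 1. State one readmission window. The outcome list counts from birth, the extraction from discharge. Extraction to 28 days after discharge always reaches day 28 of life, so a count from birth can be derived if event days are kept.
2. Keep total readmission as a descriptive outcome. Report it separately before and after a landmark at about day 10 (antibiotic start up to 72 hours after birth under Primary outcome, plus a 7-day course). Base the pre/post comparison on the landmark to day 28.
3. Beside it, compare an event that excludes readmission itself and is counted in hospital or at home within 28 days after birth. It is the first of: re-initiation of antibiotics after stopping; a newly added intravenous agent, or return to the intravenous route, more than 48 hours after treatment start; or a new positive blood culture. Tabulate return to the intravenous route separately, because it arises almost only after implementation.

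The cost is outcome and analysis wording. Agents, duration, cultures and re-initiation are in the extraction list, and route is measured for the primary outcome; confirm that dates and route are available per neonate. The downsides are small. An agent or route change is an imperfect proxy that misses a ward deterioration managed on the same agents, and the window after the landmark has fewer events. The fix does not address the sampling of treated neonates only, which should be stated as a limit on any safety reading.
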